## Abstract

**Background:**

When children are unable to safely live at home with their parents, contact between these children and their parents is considered, in most cases, important for maintaining children’s sense of identity and relationships with their parents. However, the research evidence on contact is weak and provides little guidance on how to manage contact and when it is beneficial or potentially harmful. The evidence in relation to contact interventions with parents and their children who are to remain in long-term care is the most limited. A small number of studies have been identified where interventions which were therapeutic, child-focused and with clear goals, particularly aimed at preparing and supporting parents, showed some promising results. This trial aims to build on the existing evidence by trialling an enhanced model of contact in multiple sites in Australia.

**Methods/Design:**

This study is a cluster randomised controlled trial of an enhanced contact intervention with children in long-term care who are having supervised contact with their parents. Intervention sites will implement the kContact intervention that increases the preparation and support provided to parents in relation to contact. Baseline and follow-up interviews are being conducted with parents, carers and agency workers at intervention and control sites. Follow-ups interviews will assess whether there has been an increase in children’s emotional safety and a reduction in distress in response to contact visits with their parents (the primary outcome variable as measured using the Strength and Difficulties Questionnaire), improved relationships between children and their parents, improved parental ability to support contact, and fewer contact visits cancelled.

**Discussion:**

By increasing the evidence base in this area, the study aims to better guide the management and supervision of contact visits in the out-of-home care context and improve outcomes for the children and their families.

**Trial Registration:**

Trial registered on 7 April 2015 with the Australian New Zealand Clinical Trials Registry ACTRN12615000313538

## Introduction

When children are unable to safely live at home with their parents, contact between these children and their parents is considered, in the majority of cases, important for maintaining children’s sense of identity and relationships with their parents, and as a means of enhancing their emotional, behavioural and intellectual development [1, 2]. However, the research evidence on contact is weak and provides little guidance on how to manage contact, and for which children and in what circumstances it is beneficial or potentially harmful [2–4]. One the one hand, good quality contact in conjunction with other constructive professional intervention has been found to promote positive outcomes for children and is positively correlated with children’s current wellbeing and stability [1, 5]. On the other hand, contact can be disruptive: it can prevent children developing a sense of permanence, cause additional emotional strain on children, and can increase conflicts between parents, carers and children [1, 6, 7]. It is important, therefore, that contact service providers and agencies with the parental responsibility for children in the care of the state minimise the possibility that these children will experience further distress as a result of their family contact visits [8]. Neither should contact contribute to further adverse outcomes for their mothers and fathers which may, in turn, lead to a loss of contact with their children. Designing and supporting contact interventions that improve outcomes for children and their families is therefore vital.

The study discussed in this paper was designed to address gaps in the research evidence by developing and trialling an evidence-informed model of delivering contact. The focus of this study is on supervised contact for children aged 0 to 14 years in long-term foster or kinship care.

## Background

Direct contact (the focus of this research) refers to the planned face-to-face visits with parents or significant others when parents are no longer providing primary care to the child or young person [9]. Contact may also be referred to in the literature as ‘access’ or ‘visitation’. The legislation governing the care and protection of children in Australia supports continued contact between children in care and their parents, as does the *United Nations Convention of the Rights of the Child*, Article 9 [10] which supports the rights of children to maintain personal relationships with their parents, unless this would not be in the best interests of the child.

Contact may be supervised if there are particular concerns about the ongoing safety of the child and the type of abuse that led to the child being removed [11, 12]. Other factors such as the age of the child and their relationship with the parents may also be influential in making decisions about supervision [1]. Over time the need for and appropriateness of supervision may change, however, as the placement becomes established and the child’s age increases and their vulnerability decreases [8].

Supervised contact refers to contact in which interactions and conversations between the parent and child are closely monitored by a nominated person, such as a relative or carer, or via an agency such as a contact service [13]. Some authors have noted that there is no common understanding of the concept, definition, or purpose of supervised contact amongst service providers working in the child protection system [14]. Formal contact supervisors may either be there to simply observe and take notes about the interactions between parent and child, while ensuring safety, or they may have a more engaged role that supports and enhances parent–child interactions [4]. Supervised contact visits have been described as providing a therapeutic experience, an evaluative method for assessing parental bonding, or a proactive method of enhancing poor parenting skills [8, 15]. Currently there are no coherent and empirically-based theory and guidelines with which to judge the quality of contact, nor criteria for evaluating what occurs during meetings between children and their parents [4].

It has been reported in the literature that between 56 % and 94 % of children in foster and kinship care have some direct contact with their parents, although this generally reduces over time [2, 16–18]. A small number of studies have reported that around 50 % of children in kinship care have this contact supervised, while higher proportions of children in foster care have their contact supervised (56-67 %) [2, 17, 18].

### Contact interventions

The few contact interventions identifiable in the literature tend to focus on contact for families for whom reunification of the child and their parents is the goal. The evidence in relation to contact interventions with parents and their children who are to remain in care is more limited. A small number of studies have been identified where interventions which were therapeutic, child-focused and with clear goals showed some promising results. These interventions included components such as: clarifying the purpose of contact visits; providing greater support and structure to parents, children, caseworkers and carers; and facilitating, planning and increasing the preparation for all of those involved [19–22]. Findings from qualitative studies indicate that support via training and/or emotional support, facilitating planning, and enhancing communication for all those involved in providing family contact are valued and may lead to higher quality contact [23–25].

This paper describes the design and protocol for the kContact study, a cluster randomised controlled trial being conducted in Victoria and the Australian Capital Territory (ACT), Australia. The kContact intervention developed in the first stage of this study will be trialled using a prospective design that compares (i) children and young people who receive treatment as usual (standard contact) with (ii) children and young people receiving the kContact intervention, at baseline and nine months. It will be innovative for the child welfare field in its use of both qualitative and quantitative components and its use of multiple study informants (experts, children, parents, carers, workers and the study’s partner organisations delivering the contact services).

### Aim and hypotheses

The aim of the trial is to test the effectiveness of an enhanced model of managing contact for children in long term out-of-home care and their parents (the kContact intervention).

It is hypothesised the intervention will:i)increase children’s emotional safety and reduce their distress related to contact (primary outcome variable);ii)improve relationships between children and their parents;iii)improve the ability of parents to support children in the context of contact visits;iv) reduce the proportion of contact visits cancelled within the nine month follow-up period in comparison to a control group.

## Study Design

### Trial registration

This trial was registered with the Australian and New Zealand Clinical Trials Registry (ACTRN12615000313538)

### Ethics approval

Ethics approval was obtained from the Australian Catholic University’s Human Research Ethics Committee (HREC), and ratified by the University of Melbourne HREC. Approvals were also obtained from the Victorian Government Department of Health and Human Services (DHHS), ACT Community Services Directorate and our non-government partner agencies to conduct the study within their organisations.

### Recruitment of agencies and programs

Ten government and non-government agencies providing foster and kinship care services, which included the supervision of contact for children in care, in either ACT or Victoria agreed to partner with the researchers in contributing towards and applying for research funds to conduct the kContact study. All agencies had agreed to being randomised to either the intervention or control group.

Because of the variation in agency size, the number of locations and range of programs (foster and kinship care) provided by some of these agencies, the ten agencies were divided into 18 programs for the purposes of the study: these 18 programs form the study clusters.

### Randomisation of programs (clusters)

Allocation of the programs (clusters) was undertaken using the following randomisation process. Meetings were held in both jurisdictions with representatives of all the participating agencies present, to ensure the transparency of the process. The program sites were paired according to the size of the program. To minimise selection bias, for each of the nine pairs an independent researcher randomly selected each site (using opaque, identical, sealed envelopes) to either the intervention group or the control group, by picking envelopes out of a box. This resulted in the selection of nine intervention and nine control sites across the two jurisdictions.

As is standard in a cluster randomised trial, the intervention will be implemented across the intervention sites and all clients of that program will receive the intervention whether they are actively recruited into the study or not. Staff involved in providing supervised contact for children and their parents in the intervention sites will be provided with specific training, support, a manual and resources by the kContact team. The control group sites will continue to provide supervised contact services to children and their parents as outlined in their case management plan and their agreed contact arrangements, or “treatment as usual”. Control group sites will be provided with training and resources to adopt the intervention, should they wish to, at the conclusion of the study.

### Blinding (allocation concealment)

This is an open, unmasked study. Steps have been taken, however, to ensure the separation and independence of the outcome data collection from the support of the intervention, by ensuring that the research team member providing the intervention training and monitoring the fidelity of the intervention does not collect outcome data.

### Sample size

There are no estimates of effect size on which to base our sample size calculations, as there are no trials of contact interventions published. We have made some assumptions to determine the sample size necessary to detect change in the primary outcome variables (namely, increase children’s emotional safety and reduction in their distress related to contact) using PASS software (2014). As there are no estimates available for the matching correlation, we have used a conservative approach and estimated power using an unmatched cluster randomised design [26]. Assuming an intracluster correlation coefficient of 0.06 [27] and an average cluster size of 10, randomising 18 clusters to two groups will yield 100 % power to estimate an effect size of 1.0; 72 % power to estimate an effect size of 0.5; and 39 % power to estimate an effect size of 0.33.

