### Planned analyses

Comparisons of the control and intervention groups will be made at baseline by calculating descriptive statistics to assess randomisation. Analysis for the continuous primary outcome, SDQ, will be performed using a linear mixed model to allow for the matched, clustered design of the trial. We will adjust for the baseline value and any potential confounding variables that display baseline imbalance between intervention groups. Secondary outcomes will be analysed in a similar way. For dichotomous variables, we will use a generalised linear mixed model, which extends the standard logistic regression model to account for the clustered data. The qualitative data will be coded for themes and used to add additional context to the quantitative data.

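### The sample size section calls power from an unmatched design conservative, but for the planned pair-matched analysis that holds only if the matching correlation exceeds about 0.13, for which the protocol gives no evidence

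*Protocol article*

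**What the plan says.** Under Randomisation of programs (clusters), the protocol article says "The program sites were paired according to the size of the program" and that "for each of the nine pairs an independent researcher randomly selected each site" to one group or the other. Size is the only pairing factor named.

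The Sample size section gives its inputs as follows: "Assuming an intracluster correlation coefficient of 0.06 [27] and an average cluster size of 10", with "randomising 18 clusters to two groups". It says that no estimate of the matching correlation was available, and continues: "we have used a conservative approach and estimated power using an unmatched cluster randomised design". The stated power is 100% at an effect size of 1.0, 72% at 0.5 and 39% at 0.33.

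Under Planned analyses, the primary SDQ analysis is "a linear mixed model to allow for the matched, clustered design of the trial", adjusted for the baseline value. The article does not state alpha, sidedness or degrees of freedom.

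**The concern.** Calling a power calculation conservative tells the reader that the true power is at least the stated figure. Ignoring a matching does not guarantee that. Pairing has two effects on a cluster trial. It removes whatever variance the pairs share, which raises power, and it spends degrees of freedom, which lowers it. With many pairs the second effect is negligible; with nine it is not. If the pairing factor is weakly related to the outcome, the matched analysis has less power than the unmatched calculation shows.

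The power figures therefore describe a different analysis from the one planned and are presented as a floor for it. Stated power is already below 80% at 0.5 and 0.33 SD, so readers are likely to use these figures when they interpret a null result.

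**Working it through.** **Inputs.** From Sample size: 18 clusters, average cluster size m = 10, intracluster correlation 0.06. From Randomisation of programs: nine pairs, hence nine clusters per arm. Assumed: two-sided alpha of 0.05, which the article does not state but which reproduces all three stated powers.

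**Step 1: reproduce the stated figures.**
- Variance of a cluster mean, in SD² units: 0.06 + (1 − 0.06)/10 = 0.154. Equivalently, the design effect is 1 + 9 × 0.06 = 1.54.
- Standard error of the arm difference: √(2 × 0.154/9) = 0.185.
- Noncentrality: 1.0/0.185 = 5.41; 0.5/0.185 = 2.70; 0.33/0.185 = 1.78.
- Unmatched degrees of freedom: 2 × (9 − 1) = 16.
- Power from the noncentral t distribution: 99.9%, 71.8% and 38.9%, matching the stated 100%, 72% and 39%.

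Other conventions do not match at 0.5 and 0.33 SD. A normal reference gives 77.1% and 43.0%, a t on 178 df gives 76.7% and 42.6%, and a one-sided t on 16 df gives 82.7% and 52.5%. The stated figures therefore use the full unmatched degrees of freedom.

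**Step 2: the same inputs under a strict pair-matched analysis.** Let r be the correlation between the two cluster means in a pair. The standard error becomes 0.185 × √(1 − r), and the degrees of freedom are 9 − 1 = 8.

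| Analysis | r | Power at 0.5 SD | Power at 0.33 SD |
|---|---|---|---|
| Unmatched, 16 df | not used | 71.8% | 38.9% |
| Paired, 8 df | 0 | 66.0% | 34.9% |
| Paired, 8 df | 0.05 | 68.2% | 36.4% |
| Paired, 8 df | 0.10 | 70.5% | 38.1% |
| Paired, 8 df | 0.15 | 72.9% | 39.9% |
| Paired, 8 df | 0.20 | 75.4% | 41.9% |

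At an effect size of 1.0, the paired analysis with r = 0 still has 99.7% power.

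**Step 3: break-even.** Setting paired power on 8 df equal to unmatched power on 16 df gives r = 0.129 at 0.5 SD and r = 0.122 at 0.33 SD. Matching the rounded 72% and 39% needs 0.132 and 0.126. The threshold is thus about 0.13.

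**Step 4: what that threshold asks of the pairing.** Only the between-program part of the variance can be shared within a pair, so r cannot exceed 0.06/0.154 = 0.39. Reaching 0.13 needs 0.13 × 0.154 = 0.020 of shared variance, and 0.020/0.06 is about one third. Program size would have to account for roughly a third of the between-program variance in carer-reported SDQ. The article offers no evidence on this either way.

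**Step 5: what the baseline adjustment could recover.** Suppose a baseline correlation b reduces both variance components by the factor 1 − b². This is an assumption, as the article gives no value for b. At r = 0, the loss is repaid when b² equals the break-even r: b = √0.129 = 0.36 at 0.5 SD and √0.122 = 0.35 at 0.33 SD. With b = 0.5, the paired analysis on 8 df has 78% and 44% power.

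**The case against.** The strongest reply has three parts.

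**The article does not fix 8 degrees of freedom.** It specifies a mixed model, not a paired t-test, and does not say whether pair is a fixed or a random effect. A model with a random pair effect may keep more than 8 df when the pair variance is estimated at zero. In a simulation with r = 0 that used 16 df in those cases and 8 otherwise, the pair variance was zero in about half the trials and power was 74% and 42%. This stands as a reason to treat 66% and 35% as the full-loss case. It does not rescue the claim of conservatism, because that power came with a type I error of about 6.5% instead of 5%.

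**The power calculation also leaves out the baseline adjustment, which works the other way.** This stands in full. A reader might infer that the trial's power is simply overstated unless the matching is informative. The documents do not support that: a moderate baseline correlation could bring the matched analysis back to the stated figures or above them. The like-for-like comparison, without covariate gain, is all that can be settled.

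**The article is open about what it did, and the gap is modest.** This is also fair. The unmatched design and the reason for it are disclosed, the figures are correct for that design, and power below 80% is stated plainly.

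Other stronger readings should not be drawn either. Nothing says the arm effect will be tested against a normal reference, and the choice of small-sample method may lie in an analysis plan that is not shown. Unequal cluster sizes and losses at nine months might lower power further, but the article gives no variation in recruited children per program. Nor does it say whether the average of 10 means recruited or analysed children.

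**Conclusion.** The concern holds as a correction to one affirmative claim. The stated powers are right for an unmatched comparison on 16 df. They are not shown to be a lower bound for the matched analysis that the article plans.

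On the stated inputs, a strict pair-matched analysis with r = 0 has about 66% power at 0.5 SD, 6 points below the stated 72%, and about 35% at 0.33 SD, 4 points below the stated 39%. There is no practical difference at 1.0 SD. Ignoring the matching is conservative only if r exceeds about 0.13. The article says it has no estimate of r, so it cannot claim that.

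The figures rest on a two-sided alpha of 0.05, equal clusters of 10, full loss of degrees of freedom to the pairing, and no gain from baseline adjustment. The direction of the error for the complete planned analysis, baseline adjustment included, remains open.

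**What to change.** Delete the word conservative from the Sample size section. Restate power for the planned pair-matched analysis on 8 df over a range of matching correlations. For r from 0 to 0.2, this is about 66% to 75% at 0.5 SD and 35% to 42% at 0.33 SD. If the sponsor wishes to rely on the baseline adjustment, state the baseline correlation assumed and show power with and without it.

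The cost is a sentence or two and a slightly less favourable figure at the low end of the range. The number of clusters, the number of participants, the allocation and the analysis model are unchanged.

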### Selection criteria for participants

Study participants are being recruited from the participating study sites, both intervention and control. Because the study intervention is focused on supervised contact between children in long-term care and their parents, the selection criteria developed was as follows: children aged up to 14 years in long-term care (on long-term care orders) having supervised contact with one or more parent which is managed by one of the participating agencies.

Although the major study outcomes are in reference to the study child, much of the data will be collected from other informants (namely, carers, parents and caseworkers). However, as it is important to include the voices of children about issues that affect them, as part of this study, children aged 8–14 years are being interviewed but only in the ACT as part of a PhD study. This age group was selected based on a view that 8 years is the minimum recommended age for interviewing children in the child protection system [28].

### Procedure for the identification of eligible participants

The procedure used to identify children who fit the selection criteria is as follows: participating agencies plus the ACT and Victorian government agencies developed lists of individual eligible children and their families (children aged 0–14 years in long–term out-of-home care having supervised contact through a partner agency) which were provided to the researchers, to be stored securely. To avoid duplication, only one child per family is recruited, unless two children are having separate contact with each parent. Where there is more than one eligible child having supervised contact with one parent, simple randomisation using a computer-generated randomisation table is used to select the study child.

The ACT child protection agency, who is a partner on the project, provided signed consent forms to the researchers which gives permission for carers and agency workers to be interviewed in relation to the eligible children, for children aged 8 to 14 years to be interviewed in ACT, and to provide information that will help locate the child participants for follow-up interviews. It was a requirement of the child protection department (DHHS) in Victoria that consent forms be signed by parents who have shared parental responsibility with the Department.

